### **University of Buffalo Participant compensation**

In order to increase both recruitment rate and retention, all subjects will be compensated for their travel expenses. During this time they will also be required to keep diaries, return questionnaires and provide blood and urine samples. This is considered exceptional time burden over a fairly condensed period of time. The amount of money we offer is modest (\$10 per clinic visit) and includes payment for participant travel expenses and effort. These payments will be processed every 3 months. Participants will complete vouchers at the end of each visit (required by University rules).

### **D.11 Sub-studies**

**D. 11. a.** One sub-study will be conducted in the EAGeR trial to evaluate compliance with Study Pills. The sub-study will be based on analysis of urine samples for the presence of aspirin metabolites. The evaluations will be done on a 5% sample of the women participating in the study; that is about 80 samples in total. The sampling scheme will be developed by the DCC. For the sub-study to provide the most useful information, the sampling plan needs to consider possible variability in compliance among subjects, over time and with pregnancy status of the woman. We plan to sample 30 participants in month 2, 30 in month 4 of the non-pregnancy follow-up and 20 in the second month of pregnancy. The sample will include women in both treatment arms with a ratio of about 4-5:1 of aspirin versus placebo. This condition will help maintain the masking of treatment allocation and also allow compliance evaluation for women in the placebo arm

who may be taking aspirin independently. The sampling scheme will also allow for weighting of probabilities of selection by the reported adherence of the participants.

**D.11.b** Another sub-study will evaluate the role of adipocyte cytokines in the risk for gestational diabetes. This sub-study is titled: A study of novel adipocyte cytokines and the risk of gestational diabetes mellitus.

**Background:**

Gestational diabetes mellitus (GDM) is among the most common complications of pregnancy. Approximately 3-7% of all pregnancies are complicated by GDM, resulting in more than 200,000 cases annually (1). Importantly, this number is likely to increase as the prevalence of obesity among reproductive age women increases. Recent data have shown a substantial rise in the incidence of GDM from 1991 to 2000 (2) and a doubling from 1994 to 2002 (3). Women with GDM have increased risk for prenatal morbidity and a considerably elevated risk for impaired glucose tolerance and type 2 diabetes mellitus (type 2 DM) in the years following pregnancy. Children of women with GDM are more likely to be obese and have impaired glucose tolerance and diabetes in early adulthood. Although the precise underlying mechanism is yet to be identified, insulin resistance and inadequate insulin secretion to compensate for it play a central role in the pathophysiology of GDM. The metabolic challenges related to pregnancy reveal an otherwise undetected predisposition to glucose metabolic disorders in some women.

Excess adiposity is the single most important modifiable risk factor for the development of GDM. Mechanisms linking excess adiposity to elevated risk of GDM are not completely understood, but recent evidence points to a crucial role of specific hormones and cytokines ("adipokines") secreted by the adipose tissue. A major breakthrough in understanding the link between adiposity and glucose intolerance has come from the demonstration of a cross-talk between adipose tissue and other insulin target tissues such as skeletal muscle and liver. Such cross-talk is mediated by a number of molecules that are secreted by adipocytes and act in an autocrine, paracrine, or endocrine fashion. Among those identified to date are retinol binding protein 4 (RBP4), resistin, leptin, IL-6, and adiponectin (in particular, high molecular weight adiponectin). In concert, these cytokines, or 'adipokines', are believed to adapt metabolic fluxes to the amount of stored energy. Dysregulation of this network is believed to be a critical factor in the deterioration of insulin sensitivity that accompanies adiposity.

Despite the promising role of these novel adipocyte cytokines in the pathophysiology of insulin resistance, prospective studies of these adipokines in association with EAGeR GDM risk are sparse. The majority of limited available studies are small cross-sectional studies, inferences from which were hampered due to the ambiguous temporal relation between these adipokines and GDM risk. The major aim of this project is to prospectively investigate novel biochemical markers involved in adipokine secretion as predictors of GDM. In addition, we will examine whether these associations are independent of or modified by measures of overall and abdominal adiposity (BMI and waist circumference), and whether the associations between adipokines and GDM risk are mediated through elevated plasma free fatty acids.

Study design: A nested case-control study of 200 GDM cases and 400 controls based

on longitudinal data from 2 prospective studies.

1. EAGeR Trial (PI [name]): In this study, 1600 women with a history of miscarriages will be recruited. Among them, approximately 960 women (60%) are expected to have successful pregnancy in 6 months of trying. Approximately 40-70 GDM cases are expected to result from this study. For these cases we will select 80-140 controls.

2. The National Standard for Normal Fetal Growth study (PI [name]): In this study, 2400 low risk women will be recruited. Among them, there would be 70-90 GDM cases. We will add an arm of 600 high risk pregnant women (being obese) to this study, among which there would be at least 60 GDM cases.

By combining these two studies, we expect to obtain 170-220 GDM cases. Longitudinal blood samples including before pregnancy (EAGeR trial), during the 1st, 2nd, and 3rd trimester and 6 weeks postpartum (Fetal Growth Study) will be collected.

Adding a blood collection in the 16th gestational week to the EAGeR trial will enable the investigation of changes in adipokine levels every four weeks before clinical GDM screening test (24-28 weeks), which is a crucial time window for studying the pathogenesis of GDM. The approximately 4 bio-specimens from each woman before GDM screening test will allow a greater precision in evaluating the longitudinal trend of adipokine levels and other important molecules within individual women. Moreover, the inclusion of 16 gestational week blood collection will enable the time windows for bio-specimen collection in the EAGeR trial to be comparable to those in the Fetal Growth Study, another data source for the 'Adipokines and GDM' project.

#### **Data collection and pregnancy follow-up**

The new "Week 16" visit will be identical to other pregnancy clinic visits with the same questionnaires administered and same blood and urine samples obtained. The consent for this sub-study is covered by the original consent.

## E. STUDY TIMELINE

The study duration is five years. The first 6-8 months are considered as Phase I of the study and are used for study set-up, developing and writing of the study protocol, MOP, questionnaires and developing the study's web-site and computerized data entry system and securing IRB approval. This time will also be used to obtain the study pills and all the materials needed for the study as well as the recruitment materials. Phase II of the study starts with recruitment and continues with participants' follow-up and data collection until the end of months 57. The last three months of the trial are Phase III which is the wrap-up time used for final analyses and writing of reports. The timing of the segments of the study from the start of funding is shown in Table 2 below.

**Table 2. Study phases and activities by months from start of funding**

| Phase               |       |      |        |       |        |       |        |       |        |       |       |  |
|---------------------|-------|------|--------|-------|--------|-------|--------|-------|--------|-------|-------|--|
| I                   |       |      | II     |       |        |       |        |       | III    |       |       |  |
| Year 1              |       |      | Year 2 |       | Year 3 |       | Year 4 |       | Year 5 |       |       |  |
| Time                | 0-6   | 7-12 | 13-18  | 19-24 | 25-30  | 31-36 | 37-42  | 43-48 | 49-54  | 55-57 | 58-60 |  |
| (Mos.)              |       |      |        |       |        |       |        |       |        |       |       |  |
| Task                |       |      |        |       |        |       |        |       |        |       |       |  |
| Set-up and training | 0-6   |      |        |       |        |       |        |       |        |       |       |  |
| Recruitment         | 7-40  |      |        |       |        |       |        |       |        |       |       |  |
| Active follow-up    | 8-43  |      |        |       |        |       |        |       |        |       |       |  |
| Passive follow-up   | 10-47 |      |        |       |        |       |        |       |        |       |       |  |
| Pregnancy f-u       | 8-57  |      |        |       |        |       |        |       |        |       |       |  |
| Close out           | 58-60 |      |        |       |        |       |        |       |        |       |       |  |

## **F. STUDY ADMINISTRATION**

### **Groups and subcommittees**

#### *The Steering Committee*

The Steering Committee for the trial provides leadership in ensuring the scientific integrity of the study, while conforming to the ethics and standards of practice promulgated by the American College of Epidemiology. This is in addition to adherence to protection of human subjects according to the specifications of the authorizing IRBs. The steering committee includes the principle investigators at the clinical sites and the DCC as well as the Project Officer at NICHD. This committee will make all final protocol decisions.

#### *Data and Safety Monitoring Board*

A Data and Safety Monitoring Board (DSMB) will be established to provide independent guidance to the study conduct. The members of the DSMB will include experts in relevant fields, potentially to include endocrinology, fertility, reproductive epidemiology, biostatistics and bioethics. DSMB members are appointed by the Director of the NICHD. The DSMB reports to the NICHD director through the NICHD Project Officer and the DESPR Director. The DSMB is charged with reviewing all interim data for safety and efficacy and for recommending to the Project officer any actions that should be taken to insure the ethical conduct of the trial. Results of all such reviews will be available to the investigators upon completion of the trial and unblinding. Final decisions for study continuation or discontinuation will be made by the NICHD Director. The DSMB will also have to provide periodic reports for submission to site IRB's stating the study continues and other necessary updates.

#### *Other study committees*

Additional special committees including endpoints committee and publishing committee will be established during the evolution of the trial.

## **G. STATISTICAL ANALYSIS**

### **G.1 Overview**

The EAGeR trial is designed as a multi-site randomized double blind clinical trial with two treatment arms: folic acid + aspirin compared to folic acid + placebo. A fixed sample size of 1600 randomized complete subjects is planned. Thus, for planning and statistical power computations we assume that this is the number of subjects who complete the trial and does not include dropouts.

The primary analysis plan is based on an “intention-to-treat” approach comparing the two treatment arms based on the randomized assignment, ignoring later changes in treatment. This analysis is described in Section G.2. The Haifa DCC will perform periodic partial analyses and present interim reports to the DSMB as requested, during Phase II of the trial. It is anticipated that partial analyses will be performed every 6-12 months. The final analysis will be performed upon completion of data collection and editing in Phase III of the trial. Also one full formal interim analysis is planned and the power calculations with considerations for the choice of optimal time for the analysis are given in Section G.3.

In addition to the intention to treat analysis, the Haifa DCC will engage in methodological research with the Project Officer at the NICHD. The focus is on developing statistical methods for clinical prediction models of reproductive outcomes as described in Section G.4, analysis of intermediate endpoints (Section G.5) and evaluating the effect of dropouts and compliance on the study results (Section G.6).

### **G.2 Study endpoints and intention to treat analysis**

#### **G.2.1 Study endpoints: operational definition and verification**

Study endpoints will be determined based on self-reports, self-administered pregnancy tests, clinic pregnancy tests, medical record evaluations (including routine pregnancy follow-up, ultrasound) and laboratory tests. Whenever possible, we will verify the endpoints using different sources of information. For example, a report by a woman of a positive pregnancy test will be verified against the laboratory results for urine hCG around the same date of the self-reported pregnancy. Similarly, self-reports of pregnancy loss will be ascertained by medical records (in case of a clinically recognized pregnancy) or by blood and urine tests around the same time point (in cases of early loss <12 weeks' gestation).

Operational definitions for a study outcome events are detailed in Section C.4. The sources of information for study endpoints ascertainment:

- a) Live birth – based on hospital records
- b) hCG detected pregnancy (implantation) – a self-report of a positive home pregnancy test followed by a spot urine test in the clinic and quantitative hCG evaluations in urine and serum specimens.

- c) Early loss of pregnancy (ELP) – hCG pregnancy loss will be defined as a rise of urinary HCG to  $>0.025$  ng/mL for at least 3 consecutive days followed by a decline. The rise and fall of HCG will be evaluated during the 10 days prior to the next menstrual period through day 5 of the next menstrual period. Clinically recognized pregnancy losses will be identified based on self-report followed by confirmation on ultrasound and medical records,
- d) Specific pregnancy outcomes: Cesarean section, preeclampsia, gestational age, preterm birth birthweight [small for gestational age], major neonatal complications or death, and severe post-partum maternal morbidity will be determined based on hospital records and medical chart abstraction.

All events will be reviewed and verified by a central outcome review that will be performed by the NICHD Project Officer and the Principal Investigators at the study clinical sites and the Data Coordinating Center.

### G2.2 Intention to treat analysis

The primary analysis of the clinical trial will be “intent to treat” (ITT) analysis based on the total cohort of randomized patients. This approach will be applied to the primary endpoint (live birth) as well as designated secondary endpoints. The difference between the incidence rates of live births for the two treatment groups will be examined by a two-sided test based on the standard Z-score (using the normal approximation to the binomial distribution). The common null hypothesis states that the effect of aspirin on the outcome is null compared to the placebo.

The secondary objectives (as described in Section A) with binary endpoints will be analyzed similarly as comparison of proportions. For binary outcomes such as pregnancy, the time to event may be of interest. In this case, survival analysis methods will be applied with the log-rank test for comparison of the two study treatment groups. For continuous outcome such as birthweight either parametric or non-parametric methods will be used as appropriate. If transformations to approximate a normal distribution are feasible, they will be carried out prior to the parametric analysis. The normality of the data will be examined both graphically using Q-Q plots and by formal tests (Wilks- Shapiro test). For data (either on original or transformed scale) assumed to be normally distributed the comparison of the two treatment groups will be carried out by a t-test. Alternatively if a non-parametric test is required, the Wilcoxon-Mann-Whitney test will be used.

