The trial will be conducted at two clinical sites, the University of Utah in Salt Lake City, Utah and the University at Buffalo in Buffalo, New York. The Utah site includes four medical centers and the Buffalo site will be conducted at a free standing research clinic at the University enrolling participants from the western NY region. Henceforth the term “clinical center” refers to each of the five clinics participating in the trial at the two sites. The study will take a total of 5 years to complete including start up activities (Phase I), recruitment and follow-up of pregnancy outcomes in all subjects (Phase II) and wrap-up and analysis (Phase III). Participants will be recruited from throughout the community and enrolled over approximately a three to four year time period. By the end of the study, it is expected the University of Utah will have enrolled 1100 complete subjects, two thirds of the study population, and the University at Buffalo will have enrolled 500 complete subjects. **To be considered a complete subject, participants need to complete at least 90% of their scheduled clinic visits.** The number of required visits will depend on the participant’s length of follow-up in the trial.

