#### ***D.5b. Randomization Protocol***

Randomization of subjects will be carried out to obtain the 1:1 allocation ratio between the treatment and placebo arms. Randomization will be stratified by center and by eligibility criteria group. Two eligibility groups will be considered: group I including all women who have had only one spontaneous abortion in gestation week <20 and within the last 12 months, no more than one live birth in the past and no pregnancy losses occurring on or beyond 20 completed weeks of gestation; group II includes women who do not fit group I but are eligible by the modified criteria. A computer algorithm will create the random assignment to one of the treatment arms based on random permuted blocks design with randomly varied block size.

The random sequence of treatment assignment will be linked to a pre-determined list of study ID numbers generated at the Haifa DCC for each clinical center and to a corresponding non-informative list of medication bottle numbers for the treatment assignment. This list will reside on the local computers at the DCC and a mirror copy (encrypted) will be kept in a different secured location. As soon as an allocation is done, the information will be sent automatically to the server and the master randomization file will be updated accordingly.

A list of subject Study ID numbers will be created a-priori for each clinical center. At the baseline visit, when a new participant is enrolled, a new Study ID will be automatically generated through a secured link in the study's Web-based system. In the randomization

visit, the computer system will generate the treatment assignment for the current participant and the Bottle ID number for Study Pill will appear according to the randomization scheme. A subject will not be randomized without an indication of a signed informed consent and a confirmed eligibility.

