The following Tables 3 and 4 present results of power calculations for various interim looks plans for the EAGeR trial. These demonstrate the implications of different choices for the number and timing of interim looks. We assume throughout an alpha level of 0.05 and a sample size of 1600 women divided equally to the aspirin and placebo arms of the trial. Previously published studies suggest that for the control group a probability of about 0.70 - 0.80 for live birth given pregnancy ( $P_{preg}$ ) can be expected. Further, the probability of implantation per cycle ( $P_{implant}$ ) was assumed to be constant and in the range between 0.175 and 0.25. Figure 4 shows the probability of live birth (PLB) considering six cycles of menstruation (including both active and passive follow-up):

$$PLB = P_{preg} P_{implant} \sum_{c=1}^6 (1 - P_{implant})^{c-1}$$

**Figure 4.** Probability of live birth versus implantation probability per menstrual cycle

[figure not shown]

Hence a conservative estimate for the live birth rate would be a combination of implantation rate or 17.5% per cycle and a probability of live birth given pregnancy of 70% yielding an estimated value of  $PLB = 0.479$ . The final calculations will be done after the population from which participants are drawn will be identified. A refinement of the calculation can easily incorporate non-fixed probabilities of implantation per cycle

In the following, we consider a range of probabilities for the placebo + folic acid arm of 0.46, 0.48 and 0.50. The effect of the intervention will be measured as the rate ratio (RR) of live birth in the aspirin + folic acid arm compared to placebo + folic acid. We consider effect sizes of 1.15, 1.20 and 1.25. The calculations were preformed using PASS software. Table 3 presents the resulting power for no interim looks and Table 4 shows the power for one or two interim looks for selected outcome probabilities and effect size.

**Table 3.** Power for comparing live birth rates in treatment and placebo groups with no interim looks.

| Live Birth Probability in placebo arm | Live Birth Rate Ratio to be Detected |            |      |
|---------------------------------------|--------------------------------------|------------|------|
|                                       | 1.15                                 | 1.20       | 1.25 |
| 0.46                                  | .77                                  | .96        | .99  |

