### **I.3. Subject Population**

#### **A. Women and Minorities**

Women 18-40 years of age will be recruited for participation this study. All women who have experienced a pregnancy loss in the last 12 months will be provided with information about the study. In addition, information about the study will be posted in physician offices in the form of "tear-off sheets" or study brochures. No efforts will be made to exclude any women based on minority, racial, or ethnic status. Given the focus of this particular study, women will be the only participants in this study.

Participants will be requested to complete a brief questionnaire at the time of informed consent that identifies ethnicity and racial designation(s). The participant will be asked for ethnicity first and then will be able to identify one more racial designations.

The trial is potentially open to all women who fit the inclusion/exclusion criteria. The DCC will work with the clinical sites to identify potential sources of data to characterize as best as possible the race/ethnicity composition of the population to be screened for participation in the trial. Typically, trial populations do not accurately represent the target population. However, effort will be made to direct the screening to allow a heterogeneous group to be included. The DCC will generate monthly summaries to each site with the age and ethnic composition of the population screened and the group recruited. In case a growing imbalance develops, the issue will be discussed with the clinical sites and with the project officer to come up with necessary changes in recruitment strategies to minimize exclusion of minorities for any reason. No sub-group analysis is planned but statistical modeling of the data will assess the impact of age and race/ethnicity on study endpoints.

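### Randomization is stratified by clinical center and eligibility group, but the primary and interim tests of live birth are unstratified, which makes them mildly conservative if strata differ

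*Supplement*

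**What the plan says.** Section D.5b of the protocol states: "Randomization will be stratified by center and by eligibility criteria group". Section D.5a says the same. Section C.1 uses the term clinical center for "each of the five clinics participating in the trial at the two sites", so there are 5 × 2 = 10 strata. The eligibility factor came in when Amendment 1 widened entry. It separates "group I including all women who have had only one spontaneous abortion in gestation week <20 and within the last 12 months" (with further limits on live births and late losses) from all other eligible women. Allocation uses permuted blocks to "obtain the 1:1 allocation ratio between the treatment and placebo arms".

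Section G2.2 makes the primary comparison an intention-to-treat "analysis based on the total cohort of randomized patients" and says the difference in live-birth rates "will be examined by a two-sided test based on the standard Z-score (using the normal approximation to the binomial distribution". Neither factor is mentioned. In the Interim Analysis chapter, equations (1.1) and (1.2) likewise use the overall difference in proportions with a marginal variance. The power calculation in G.3 is a plain two-proportion one: "We assume throughout an alpha level of 0.05 and a sample size of 1600 women divided equally to the aspirin and placebo arms". Covariate adjustment appears only for prediction models and secondary endpoints (G.4) and for age and race/ethnicity (I.3). No section brings center or eligibility group into the primary test.

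**The concern.** Blocked 1:1 allocation within strata balances the arms on center and eligibility group, so differences in live-birth rate between strata no longer add to the sampling variance of the risk difference. The plain Z-test still uses the marginal variance, which contains those differences. When strata differ, its standard error is therefore larger than the true one, its type I error falls below 5%, and some power is lost.

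Such differences are plausible, because the eligibility groups are defined by number, timing and recency of losses and by prior live births. Power has little margin at the smallest effect considered: Table 3 gives 0.77 and 0.81 at a rate ratio of 1.15 for placebo rates of 0.46 and 0.48, counting completers only. At stake is a small amount of efficiency that the design has already paid for. There is also a specification gap that should be closed before unblinding, since a stratified analysis chosen later would look post hoc.

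**Working it through.** **Inputs from the documents.** 800 women per arm, two-sided alpha 0.05, placebo rate p0 = 0.48, rate ratio (RR) 1.15 or 1.20 (G.3); 1:1 allocation within strata (D.5b).

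**Assumed, because the documents give no stratum rates.** Two equal-sized groups, the same RR in each, and a gap in placebo live-birth rate of 0 to 30 points centered on 0.48.

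**Step 1: the plan's own figure.** At RR 1.15, p1 = 0.552, d = 0.072 and p̄ = 0.516.
- Null SE = √(2 × 0.516 × 0.484 / 800) = 0.02499.
- Alternative SE = √((0.48 × 0.52 + 0.552 × 0.448) / 800) = 0.02492.
- Power = Φ((0.072 − 1.96 × 0.02499) / 0.02492) = 0.822, or 0.809 with a continuity correction. Table 3 states 0.81.
- At RR 1.20 the results are 0.971 and 0.967, against a stated 0.97.

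All nine cells of Table 3 reproduce within 2 points.

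**Step 2: formulas under stratified allocation,** with stratum weights w = ½ and p̄s the mean of the two arms' rates in stratum s.
- SE used by the plain test: √(2 p̄(1 − p̄) / 800).
- True SE: √(Σ w[p0s(1 − p0s) + p1s(1 − p1s)] / 800).
- SE used by a stratified test: √(2 Σ w p̄s(1 − p̄s) / 800).
- Power of either test: Φ((d − 1.96 × SE used) / true SE).
- Type I error of the plain test: 2[1 − Φ(1.96 √(p0(1 − p0) / Σ w p0s(1 − p0s)))].

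**Step 3: worked case, 20-point gap, RR 1.15.** Placebo rates are 0.58 and 0.38; aspirin rates are 0.667 and 0.437.
- SE used by the plain test 0.02499; SE used by the stratified test 0.02440 (ratio 1.024); true SE 0.02433.
- Plain power = Φ((0.072 − 0.04897) / 0.02433) = 0.828.
- Stratified power = Φ((0.072 − 0.04783) / 0.02433) = 0.840.
- Type I error of the plain test = 2[1 − Φ(1.96 × √(0.2496 / 0.2396))] = 0.0455.

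**Step 4: the range.**

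| Gap (points) | SE ratio, RR 1.15 | Plain power | Stratified power | Gain, RR 1.15 | Gain, RR 1.20 | Type I error, plain |
|---|---|---|---|---|---|---|
| 0 | 1.000 | 0.822 | 0.822 | 0.0 | 0.0 | 0.050 |
| 5 | 1.001 | 0.823 | 0.823 | 0.1 | 0.0 | 0.050 |
| 10 | 1.006 | 0.824 | 0.827 | 0.3 | 0.1 | 0.049 |
| 20 | 1.024 | 0.828 | 0.840 | 1.2 | 0.3 | 0.046 |
| 30 | 1.057 | 0.836 | 0.862 | 2.6 | 0.6 | 0.040 |

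**Step 5: simulation check.** 200,000 trials per setting with ten strata (Utah's 1100 women spread equally over four centers, Buffalo's 500 in one, two equal eligibility groups in each). Power at RR 1.15, plain Z against Cochran-Mantel-Haenszel:
- gap 0: 81.7% against 81.8%;
- gap 10: 81.7% against 82.8%;
- gap 20: 81.8% against 84.0%;
- gap 30: 82.2% against 86.0%.

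Type I error of the plain test falls from 0.048 to 0.046, 0.044 and 0.039 across these gaps, while the stratified test stays between 0.048 and 0.050. The direction agrees with the formulas. The simulated gains are somewhat larger, partly because the plain statistic is discrete: it already sits at 0.048 with no gap.

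**The case against.** The case for leaving the plan alone is that nothing in it is invalid. A conservative test protects the 5% level, and Tables 3 and 4 and the interim formulas all use the same unstratified comparison, so the planned power matches the planned test. The gain needs a gap between strata that the documents do not establish. It is negligible at modest gaps and at RR 1.20, the effect carried into Table 4. All of that stands and limits the point to a minor one. It does not remove the mismatch.

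Several stronger readings are tempting and are not supported:

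- **That type I error is inflated or Table 3 is wrong.** The error goes the other way, and Table 3 reproduces.
- **That the gain is larger.** Setting the stratified 0.840 against the 0.822 of Step 1 suggests 1.8 points at a 20-point gap. That is not like for like: stratified allocation also shrinks the plain test's true variance and lifts its power to 0.828.
- **That the confidence interval is too wide.** G2.2 specifies a test and no interval method for live birth; only the standard error in the test can be criticized.
- **That the eligibility split could test whether aspirin works better after fetal death than after early loss.** Section B.4 cites odds ratios of 1.88 and 1.24, from a retrospective non-randomized study. The split does not separate these women. Group I takes losses before week 20, and so includes fetal losses at 10 to 19 weeks as defined in C.4. Group II includes women with two early losses, or one older early loss, as well as late losses. No interaction test follows from this point.
- **That the plan rules out looking at who benefits.** The sentence "No sub-group analysis is planned but statistical modeling of the data will assess the impact of age and race/ethnicity on study endpoints" sits in the section on women and minorities. G.4 separately plans exploratory live-birth models by arm using medical history and time since last loss.

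**Conclusion.** The mismatch is real and nothing in the latest version resolves it: ten randomization strata are formed, and neither the primary nor the interim statistic uses them. The consequence is a mildly conservative test if live-birth rates differ between strata, and none if they do not. Within the assumed range of gaps, the loss runs from nothing to 2.6 points of power at RR 1.15 and never exceeds 0.6 points at RR 1.20. These figures depend on two equal groups, a common rate ratio and an overall placebo rate of 0.48. Differences between centers are not modeled and could add to the effect. This is a minor efficiency and specification point; the trial's validity is not in question.

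**What to change.** In G2.2, make the primary test a Cochran-Mantel-Haenszel test stratified by eligibility group and clinical center, and report the Mantel-Haenszel risk difference and rate ratio with it. State in advance a rule for pooling small strata, since the split between groups within centers is unknown. Both factors are fixed at randomization, so the full intention-to-treat cohort can be stratified without new data.

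Use the same stratified statistic at the interim looks. This means restating equations (1.1) to (1.3) of the Interim Analysis chapter, where the marginal σ enters both the statistic and the drift, and carrying the change into the conditional-power formulas. Tables 3 and 4 can stand as slightly conservative planning figures.

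The cost is a few sentences in G2.2, a modest rewrite of the interim formulas and a small programming change, all to be settled before unblinding.
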